The primary objective of this study is to investigate the feasibility of capturing in vivo cross-sectional images of the bladder wall in patients with bladder cancer using the newly developed MEMS-based OCT catheter. Secondary objectives are to evaluate the duration of the OCT measurements, determine the tumor stage based on OCT images and test for an association with histopathological results, determine the grade of the tumor based on OCT images and test for an association with the histopathological results, determine if the OCT catheter is able to acquire evaluable images of the bladder wall after resection of the tumor, and compare the tumor grade and stage estimated during WLC with the tumor grade and stage based on the OCT images.

This is a single-group; idea, development, exploration, assessment, and long-term (IDEAL) phase 2a (development) [25]; single-center feasibility study.

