#### Secondary End Point

The secondary outcomes include (1) duration of the OCT measurements, (2) concordance between the OCT-based diagnosis of tumor invasion and histopathological diagnosis, (3) concordance between the OCT-based diagnosis of tumor grade and the histopathological diagnosis, (4) the ability of the OCT catheter to acquire evaluable images of the resection bed, and (5) concordance between intraoperative WLC assessments and OCT findings on tumor grade and invasion.

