#### Secondary Outcomes

The duration of OCT measurements (min) will be reported as medians with IQR. Tumor invasion based on OCT images will be determined by a panel of investigators. The panel will consist of 2 urologists, 1 PhD candidate, and 1 pathologist. The panel members will independently score the OCT images and classify them based on (1) whether there is a tumor present and (2) (if present) the tumor stage. In case of disagreement, an experienced research fellow will be added to the panel, and the scoring will be discussed within this panel. Consensus will be reached when 3 of the 5 members agree. The concluding tumor invasions will be descriptively compared to histopathological outcomes, with results presented as percentages with 95% CIs. Attenuation coefficients from OCT data will be analyzed and categorized into tumor grade categories, following the World Health Organization (WHO) 1973 and WHO 2016 grading systems. A descriptive comparison of OCT-based and histopathology-based tumor grades will also be displayed as percentages with 95% CIs. Associations between tumor stage and grade, as determined by OCT and histopathology, will be tested with chi-square or Fisher exact tests, as applicable. In addition, the panel will assess OCT images of the resection beds, reporting the percentage of evaluable images with 95% CIs. Finally, the urologist’s WLC-based estimates of tumor invasion and grade will be compared to OCT findings and histopathological results, and the association will be tested with chi-square or Fisher exact tests, as applicable.

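### Three concordance end points are paired with tests of association that do not measure agreement; for white light cystoscopy versus OCT no other analysis is named

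*Protocol article*

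**What the plan says.** The target changes between sections of the protocol article.

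- **Objectives (end of the Introduction).** For stage the aim is to "determine the tumor stage based on OCT images and test for an association with histopathological results", and grade is worded likewise. For WLC and OCT the aim is only to compare them.
- **Secondary End Point.** End point 2 is "concordance between the OCT-based diagnosis of tumor invasion and histopathological diagnosis", end point 3 is "concordance between the OCT-based diagnosis of tumor grade and the histopathological diagnosis", and end point 5 is "concordance between intraoperative WLC assessments and OCT findings on tumor grade and invasion".
- **Statistical Methods, Secondary Outcomes, OCT versus histopathology.** For stage: "The concluding tumor invasions will be descriptively compared to histopathological outcomes, with results presented as percentages with 95% CIs". Grade gets a similar descriptive comparison. A test is then added: "Associations between tumor stage and grade, as determined by OCT and histopathology, will be tested with chi-square or Fisher exact tests, as applicable".
- **Statistical Methods, Secondary Outcomes, WLC.** The urologist's WLC estimates "will be compared to OCT findings and histopathological results, and the association will be tested with chi-square or Fisher exact tests, as applicable". No percentage or interval is given for this comparison.

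No agreement statistic is named anywhere, and the percentages for end points 2 and 3 are not identified as percent agreement.

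**The concern.** WLC, OCT and histopathology each rate the same tumor, and the end point asks whether the ratings match. A chi-square or Fisher test takes independence of the two ratings as its null hypothesis. It gives no special role to the diagonal of the table, where the ratings match, so swapping the OCT labels leaves the p-value unchanged. It also ignores the ordering of stage and grade.

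Two misreadings follow. A small p-value may be taken as evidence that OCT agrees with histopathology. A large one may be taken as evidence that it does not, when nearly all tumors were classified alike but one category was rare. The article says that its findings will inform sample size calculations for later studies and that a diagnostic accuracy trial is the next step. Such a trial needs agreement, sensitivity and specificity with intervals, and an association p-value supplies none of these.

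**Working it through.** The article gives no alpha, power or expected stage and grade mix for these end points, so there is no figure of its own to reproduce. The check uses illustrative tables. Their sizes are 15 and 25, the stopping number and the maximum in Sample Size and Enrollment, plus 20 in between. The counts are assumptions, with one tumor per patient. Rows are histopathology and columns are OCT; the same arithmetic applies to WLC against OCT.

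**Formulas.** Agreement po = diagonal total / n. Kappa = (po − pe)/(1 − pe), where pe is the sum over categories of (row share × column share). Fisher p is two-sided. CIs are Clopper-Pearson.

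**1. Same p-value for perfect and for zero agreement**

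| Table | Fisher p | Agreement (95% CI) | Kappa |
|---|---|---|---|
| n = 15, always right [[8,0],[0,7]] | 0.00016 | 15/15 (78.2–100%) | 1.00 |
| n = 15, always wrong [[0,8],[7,0]] | 0.00016 | 0/15 (0–21.8%) | −0.99 |
| n = 25, always right [[13,0],[0,12]] | 1.9 × 10⁻⁷ | 25/25 (86.3–100%) | 1.00 |
| n = 25, always wrong [[0,13],[12,0]] | 1.9 × 10⁻⁷ | 0/25 (0–13.7%) | −1.00 |

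By hand for n = 15: only one of the C(15,7) = 6,435 arrangements is as extreme as the one observed, so p = 1/6,435 = 0.00016 in both cases. For 20 tumors, [[0,10],[10,0]] gives p = 2/C(20,10) = 2/184,756 = 0.00001 at 0% agreement. Chi-square behaves in the same way: 15.0 in both n = 15 tables and 25.0 in both n = 25 tables.

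**2. High agreement, non-significant p-value**

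| Table | Fisher p | Agreement | Kappa |
|---|---|---|---|
| n = 20, [[18,1],[0,1]] | 0.10 | 19/20 = 95% | 0.64 |
| n = 15, [[12,1],[1,1]] | 0.26 | 13/15 = 86.7% | 0.42 |
| n = 25, [[21,2],[1,1]] | 0.23 | 22/25 = 88% | 0.34 |
| n = 15, [[14,0],[0,1]] | 0.067 | 15/15 = 100% | 1.00 |

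First row by hand: the single tumor in the rare histopathology category falls among the two OCT calls of that category with probability 2/20 = 0.10. po = 0.95; pe = 0.95 × 0.90 + 0.05 × 0.10 = 0.86; kappa = 0.09/0.14 = 0.64. In the last row p = 1/15 = 0.067 although every tumor agrees.

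**3. Why percent agreement should not stand alone**

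If OCT puts all 15 tumors in the common category and histopathology has 12 and 3 ([[12,0],[3,0]]), agreement is 12/15 = 80% (51.9–95.7%), but kappa is 0 and OCT detects 0 of the 3 tumors in the rare category. Fisher p is 1 and the chi-square statistic is undefined.

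**The case against.** **Percentages are already planned for two of the three end points.** This stands. For OCT versus histopathology, the descriptive percentages most naturally read as agreement, and total discordance would then appear beside the p-value. A reader might infer that the plan reports no agreement at all, but the text does not support that for end points 2 and 3. It does leave the percentage unnamed, and the defense does not reach end point 5.

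**The test matches the objective.** For OCT versus histopathology the objectives do speak of testing an association. This explains the test but does not resolve the mismatch, because the end points drawn from those objectives are called concordance.

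**An OCT that is always wrong is artificial.** Agreed. It only shows what the test ignores. The tables in part 2, where one category dominates, are the more realistic hazard.

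**Clustering.** A reader might infer that the plan treats several tumors from one patient as independent. The article does not say so. It excludes patients with more than 5 tumors, so one patient may contribute up to 5, and specimens are numbered by tumor. The unit for these tests is not stated, and that detail may sit in the full protocol or analysis plan. It is a risk to cover in the wording, not a demonstrated error.

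**These are exploratory outcomes.** This also stands. The study is a single-group feasibility study, its primary outcomes carry no tests, and no decision rule uses these p-values.

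**Conclusion.** The point holds, to different degrees. For end points 2 and 3 the association p-value is a misleading addition to percentages that would show discordance if they are percent agreement. For end point 5 the association test is the only analysis named, so the article specifies no estimate of concordance. At the planned size the p-value can be 0.00016 at 0% agreement and 0.10 at 95% agreement. These values come from assumed tables with one tumor per patient, and they show what the test can do, not what the trial will find.

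A reader might infer that the trial's main conclusion is at risk. It is not: the primary feasibility outcomes do not use these tests. The point should be fixed, but it is not critical.

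**What to change.** In Statistical Methods, Secondary Outcomes, for end points 2, 3 and 5:

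- Use one result per tumor and make percent agreement with an exact or Wilson 95% CI the stated analysis. These intervals keep a sensible width at 0% or 100% agreement, where a patient bootstrap collapses to zero width.
- Allow for several tumors per patient, for example with a sensitivity analysis using one tumor per patient.
- Add kappa as support, weighted where stage or grade is ordered.
- Report sensitivity and specificity of OCT against histopathology, for instance invasive versus not and high versus low grade.
- Drop the chi-square and Fisher tests, or label them as not measuring concordance, and align the word association in the objectives with the end points.
- A McNemar-type paired table may be added to compare the accuracy of OCT and of WLC against histopathology. It should not serve as the measure of WLC–OCT concordance.

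The cost is wording and a small amount of programming, with no new data. CIs will be wide at 15 to 25 patients, and kappa is unstable when one category dominates. The change is best settled before OCT readings are cross-tabulated with histopathology.

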#### OCT Measurements

During the standard TURBT procedure, the OCT measurements will be performed. After the inspection of the bladder and before the resection of the identified bladder tumors, the OCT catheter will be inserted through the working channel of the rigid resectoscope. The tumors will then be imaged with the OCT catheter tip at approximately 1 cm from the tumor. Approximately 5 measurements will be performed for each suspected lesion and tumor and 3 for a selected region of normal bladder wall. When the OCT measurements are finished, the OCT catheter is removed from the bladder, and the urologist will continue with the standard procedure. The resection of the tumors is performed according to standard care. However, the pathology specimens of each separate tumor will be collected and numbered according to the tumor numbers used during the OCT measurements and sent to the pathologist. After completion of the resection, the OCT catheter will be reinserted through the working channel of the rigid resectoscope, and approximately 3 OCT measurements will be performed on each resection bed. After these measurements, the OCT catheter will be removed from the bladder, and the urologist will continue with the standard procedure (Figure 1).

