Robust data management protocols will be implemented to ensure data accuracy, security, and traceability. Data entry, coding, and security procedures will be conducted within Castor Electronic Data Capture, incorporating an audit trail to track all modifications. Paper-based case report forms will be securely stored, signed, and archived, while electronic data will be subject to automated validation procedures. Univariate data validations will be embedded within the Castor system, whereas multivariate validations, derivations, and calculations will be incorporated where applicable and documented in a dedicated data validation and derivation plan. The comprehensive data management strategy is outlined in this study’s data management plan. In accordance with regulatory requirements, all participant data will be securely retained for a period of 15 years.

Missing data will be descriptively reported and discussed. Missing OCT measurements will be reported as part of the main outcomes. Missing histopathological data are not expected; in case of missing data, it will be described in the secondary outcomes section.

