### Statistical Methods

#### Primary Outcomes

Procedural feasibility will be achieved if images of both the tumor and normal bladder are obtained in more than 60% of the patients. The feasibility based on OCT imaging will be assessed by determining the percentage of images suitable for diagnosis out of the total number of images obtained in all patients. A panel, consisting of 2 urologists and 1 PhD candidate, blinded to clinical information, will individually analyze the OCT images. They will determine if the OCT images are suitable for diagnosis. The OCT measurements will be scored as suitable if (1) tissue is observed on the OCT image, (2) the tissue is within the focus range of the OCT, and (3) no movement artifacts are observed in the image. In case of disagreement, an experienced research fellow will be added to the panel, and the scoring will be discussed within this panel. Consensus will be reached when 3 of the 4 panel members agree. The data will be described and presented as percentages with 95% CIs. No statistical tests will be performed.

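### The resection-bed end point is an ability to acquire evaluable images, but its only planned summary is a percentage of images, which does not respond to beds where no image was acquired

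*Protocol article*

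**What the plan says.** The last-but-one secondary objective in the Introduction is to "determine if the OCT catheter is able to acquire evaluable images of the bladder wall after resection of the tumor". The Secondary End Point section lists it as item 4: "the ability of the OCT catheter to acquire evaluable images of the resection bed". Under OCT Measurements, the catheter is reinserted after resection and "approximately 3 OCT measurements will be performed on each resection bed". The same section has specimens numbered to match the tumor numbers used during imaging.

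The analysis is given once, under Secondary Outcomes: "the panel will assess OCT images of the resection beds, reporting the percentage of evaluable images with 95% CIs". No denominator is named, and no summary per bed or per patient is given.

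Two other places bear on the point. Under Primary Outcomes there is a patient-level criterion, "Procedural feasibility will be achieved if images of both the tumor and normal bladder are obtained in more than 60% of the patients", and a separate image-level measure, the "percentage of images suitable for diagnosis out of the total number of images obtained in all patients". On missing data, Data Collection and Management says "Missing data will be descriptively reported and discussed" and "Missing OCT measurements will be reported as part of the main outcomes".

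**The concern.** The end point asks whether evaluable images can be acquired after resection. That can fail in two ways: an image is recorded but is not evaluable, or no image is recorded at all (the catheter is not reinserted, or imaging is given up before anything is captured). A panel can score only images that exist, so the planned percentage captures the first kind of failure and not the second.

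For tumor and normal wall the protocol treats these as two questions, with one criterion per patient and one per image. The resection bed gets only the per-image one, and the patient-level criterion does not extend to it.

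At stake is how one secondary result is read. A high percentage could be taken as evidence that beds can usually be imaged when it shows only that the images obtained were usually good. The Sample Size and Enrollment section says the findings will inform the sample size of later studies, so an acquisition rate that leaves out failed acquisitions could be carried forward.

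**Working it through.** The documents give no target, threshold or expected number of beds for this end point, so there is no planned figure to reproduce. The check is whether the planned statistic moves when beds cannot be imaged.

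**Input from the protocol:** about 3 measurements per bed (OCT Measurements).

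**Assumptions, not in the documents:** B = 20 beds in total; k of them imaged, with k = 20, 16, 12 or 8; exactly 3 images per imaged bed; E evaluable images, set to about 90% of those obtained and rounded to whole images; every imaged bed yields at least one evaluable image, which makes the per-bed figure a ceiling. Intervals are exact (Clopper-Pearson) 95% intervals. The per-image intervals treat images from the same bed as independent.

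**Formulas:**
- planned percentage, read as a share of images obtained: E / (3k)
- share of planned images: E / (3B)
- ceiling for the share of beds with at least one evaluable image: k / B

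| Beds imaged | Planned percentage | Share of planned images | Per-bed ceiling |
|---|---|---|---|
| 20 of 20 | 54/60 = 90.0% (79.5 to 96.2) | 54/60 = 90.0% | 20/20 = 100% (83.2 to 100) |
| 16 of 20 | 43/48 = 89.6% (77.3 to 96.5) | 43/60 = 71.7% | 16/20 = 80% (56.3 to 94.3) |
| 12 of 20 | 32/36 = 88.9% (73.9 to 96.9) | 32/60 = 53.3% | 12/20 = 60% (36.1 to 80.9) |
| 8 of 20 | 22/24 = 91.7% (73.0 to 99.0) | 22/60 = 36.7% | 8/20 = 40% (19.1 to 63.9) |

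The planned percentage stays between 88.9% and 91.7% while the per-bed ceiling falls from 100% to 40%. With 15 or 30 beds in total the pattern is the same: the planned percentage runs from 88.9% to 90.7% over the same range of imaged beds.

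**Which failures count.** Take the 12-of-20 row. If the other 8 beds give no image, the planned percentage is 32/36 = 88.9%. If they give 3 recorded but unusable images each, it is 32/(36 + 24) = 32/60 = 53.3%. In both cases 12 of 20 beds succeed. The result therefore depends on whether a failed attempt left a recording.

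**Can a count of missing measurements repair it?** Not without bed identifiers. Six missing measurements could be two beds with none (2 × 3 = 6) or six beds that each lack one (6 × 1 = 6). In the first case two beds failed; in the second every bed may have succeeded. The planned number per bed is also only approximate.

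**The case against.** The strongest reply is that unimaged beds need not vanish from the report. The protocol promises that missing OCT measurements will be reported and missing data described. With tumors numbered, an unimaged bed is recognisable, and a reader given both pieces could recover the per-bed share. A reader might infer from the planned percentage that the trial cannot show whether beds can be imaged; the documents do not support that. What remains is that the missing OCT measurements are assigned to the main outcomes, neither primary component names the resection beds, and nothing brings missing beds into the end point 4 percentage or its interval.

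Other parts of the reply also stand:

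- The denominator is an inference. The wording about all images obtained belongs to the primary image measure; for the beds no denominator is given.
- A reader might also infer that failures are excluded by construction, or that the figure is always too high. Neither follows. Bleeding or a poor view may still leave recorded images, and those lower the percentage. When every bed is imaged, the per-bed share can exceed the per-image one (100% against 90.0% in the first row).
- The contrast with the primary outcome is not clear-cut. The sample size text refers to patients with technically successful measurements, so it is uncertain how far failures enter the patient-level criterion either.
- Nothing in the documents suggests how many beds would go unimaged.

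It can also be said that an article may leave unit and denominator to an analysis plan. That would answer a complaint about missing detail. Here the article does name a statistic and its unit, and that statistic covers only part of the stated end point.

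**Conclusion.** The point holds in a limited form. Read as a share of images obtained, the planned percentage does not by itself measure the ability to image resection beds. It reflects image quality once an image has been acquired and is unchanged by beds with none. The planned reporting of missing measurements mitigates this only in part.

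Under the assumptions above, a planned figure near 90% is compatible with a per-bed success of at most 100%, 80%, 60% or 40%. These figures show what the statistic allows; they do not predict this trial, since every bed count and rate is assumed.

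The end point is secondary and descriptive, with no threshold and no decision attached. A reader might infer that the feasibility conclusion is at risk, but both primary criteria are defined separately from this end point. It is best treated as a cheap improvement.

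**What to change.** In the Secondary Outcomes text:

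1. State the denominator of the per-image percentage.
2. Summarise end point 4 as the proportion of resected tumors whose bed yields at least one evaluable image, with a 95% CI, and give the same proportion for patients who underwent resection.
3. Count beds that were not imaged, or that gave no evaluable image, as failures, and list the reasons.
4. Keep the per-image percentage with its CI as a supporting figure on image quality.

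The cost is wording. Tumors are already numbered, so the per-bed denominator exists and no added imaging is needed. The downside is that the reported percentage may be less favourable.

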### Monitoring

#### Data Monitoring

Data monitoring will be conducted by the Clinical Monitoring Center of Amsterdam UMC. The clinical research associates of the Clinical Monitoring Center operate independently of both the study and the research team, ensuring unbiased oversight. The monitoring committee is responsible for verifying that the rights and well-being of participants are protected; the collected study data are accurate, complete, and verifiable against source documents; and the study is conducted in accordance with the approved protocol, applicable laws, and regulatory requirements. The study-specific monitoring schedule and procedures are documented in a signed monitoring plan.

